## Abstract

**Method and design::**

In this pilot cross-sectional study, we will enroll 115 Chinese participants aged 30 to 75 years with ACS. Blood sample will be obtained after the first maintenance dose of aspirin and clopidogrel during morning time. Serum PCSK9 will be measured by an enzyme-linked immunoadsorbent assay. Platelet reactivity will be assessed by; Platelet activation (P-selectin and GPIIbIIIa expression using flow cytometry) and; Platelet aggregation using light transmission aggregometry in response to various stimuli. On-treatment platelet reactivity is measured by adenosine diphosphate-induced platelet aggregation. Binding of ox-LDL to platelet will be evaluated by flow cytometry. Spearman correlations will be used to determine association of serum PCSK9 with platelet functional parameters and platelet-ox-LDL binding. Additionally, continuous PCSK9 levels will be categorized into tertiles of equal size to investigate its association with on-treatment platelet reactivity.

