Proprotein convertase subtilisin/kexin type 9 (PCSK9) fosters the degradation of LDL receptors, suppresses LDL clearance and subsequently raises circulating LDL and ox-LDL levels.^[10]^ A clinical trials has demonstrated that PCSK9 inhibition efficiently reduces recurrent cardiovascular events in ACS patients,^[11]^ which is considered largely LDL-dependent. Indeed, preliminary data also indicates other atherogenic mechanisms mediated by PCSK9 that are independent from lipid metabolism, several of which may affect platelet reactivity and thrombogenesis.^[12]^ In PCSK9^-/-^ mice, plasma level of soluble P selectin, a platelet activation biomarker,^[13]^ was significantly lower than that in control mice.^[14]^ This finding was supported by another study showing reduced FeCl_3_ injury-induced carotid artery thrombosis and platelet P selectin expression in PCSK9^-/-^ mice versus control.^[15]^ Whereas mechanistical data regarding PCSK9-mediated regulation of platelet reactivity is so far limited.

ox-LDL binds to platelet via lectin-like oxidized low-density lipoprotein-1 (LOX-1), a class E SR,^[16]^ and this interplay contributes to ox-LDL-mediated platelet hyperactivity and facilitates inflammation-driven atherothrombosis.^[17]^ Interestingly, upregulation of PCSK9 potently stimulates LOX-1 expression and ox-LDL uptake in macrophages in an inflammatory milieu.^[18]^ The above-mentioned clues support a hypothesis that PCSK9 may also be involved in modulating ox-LDL-platelet interplay, which may be associated with PCSK9-mediated regulation of platelet reactivity. This cross-sectional study will demonstrate serum PCSK9 level and its relationship with platelet reactivity and platelet-ox-LDL binding in Chinese ACS patients to address these knowledge gaps. We present the protocol in accordance with the Standard Protocol Items: Recommendations for Interventional Trials reporting checklist.

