#### 2.2.5. Statistical analysis.

Categorical variables will be reported as counts (percentage). Distribution of continuous variables will be assessed by the Kolmogorov-Smirnov test. Normally-distributed continuous variables will be expressed as mean ± SD. Non-normally distributed continuous variables will be expressed as median and interquartile range (IQR). Comparisons between the groups will be performed by Pearson chi-squared test, analysis of variance or Kruskal-Wallis test, as appropriate. The association of PCSK9 levels with platelet reactivity and ox-LDL-platelet binding will be evaluated by Spearman rank test. For further analysis, we will divide the cohort into tertiles of PCSK9 values. univariate and multivariate logistic regression will be used to analyze the association between PCSK9 levels with on-treatment platelet reactivity. All tests will be 2-sided with an alpha level of 0.05. Analysis will be performed using SPSS version 20.0 (SPSS Inc., Chicago, Illinois).

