Preclinical studies have demonstrated that PCSK9 directly enhances platelet activation and in vivo thrombosis.^[36,30]^ Accordingly, Cammisotto et al^[37]^ found reduced platelet activation in patients with familial hypercholesterolemia after PCSK9 inhibitors administration, which was mechanistically linked to modulation of ox-LDL pathways. Indeed, during the inflammatory and oxidative processes of plaque rupture, the prothrombotic ox-LDL is generated from the modification of LDL by phospholipid oxidation.^[38]^ These observations prompt the hypothesis that PCSK9 may potentiate platelet reactivity via regulating ox-LDL-platelet interplay in the setting of ACS. Results from in vivo models revealed that ox-LDL, as a high-affinity ligand for platelet SR (e.g. LOX-1, CD36), facilitates platelet activation via binding to platelet surface.^[39]^ Interestingly, PCSK9 increased the expression of LOX-1 and ox-LDL uptake in macrophages in an inflammatory milieu.^[18]^ Whether PCSK9 is involved in the regulation of ox-LDL-platelet binding has never been evaluated in clinical settings. To this end, the association of serum PCSK9 and platelet-ox-LDL binding, an important mechanism for platelet-ox-LDL interplay, will also be explored in ACS patients.

Several limitations should be considered in this study. As this is by far the first analysis addressing the association of circulating PCSK9 with platelet reactivity and with platelet-ox-LDL binding in ACS Chinese cohort, we aim to recruit patients from a single center to achieve preliminary results. Given the limited sample size the intrinsic shortcomings of the cross-sectional design, future large prospective studies are warranted to confirm our findings. We notice that there are mounting evidence showing the direct effect of PCSK9 on platelet function in experimental conditions.^[18,30]^ In order to translate the observations into clinical settings, we emphasize to investigate the serum PCSK9 and its correlation with platelet reactivity using multiple assays, with additional goal to provide mechanistic insight from the perspective of platelet-ox-LDL interplay. If positive results are achieved, future studies are needed to unravel pathways downstream of ox-LDL-platelet binding to underlie the mechanism of PCSK9-mediated platelet activation.

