## 4. Conclusions

Several preclinical clues have suggested that beyond the role in LDL metabolism, PCSK may be involved in regulating of platelet function. To address the knowledge gaps, we aim to evaluate circulating PCSK9 levels and unravel its association with platelet reactivity in a Chinese ACS cohort. If positive results are obtained, the observations would reinforce the concept of PCSK9-mediated modulation of platelet activation in a clinical setting. Moreover, we will reveal possible relationship between PCSK9 level and ox-LDL-platelet binding, an important mechanism underlying ox-LDL-induced platelet hyperactivity, to provide mechanistic insight into PCSK9-mediated platelet activation.

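### The promised mechanistic insight rests on two PCSK9 correlations; the stated analyses do not relate ox-LDL binding to platelet reactivity in the study's own patients

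*Protocol article*

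**What the plan says.** The path appears twice. The Introduction puts it as a hypothesis that "PCSK9 may also be involved in modulating ox-LDL-platelet interplay, which may be associated with PCSK9-mediated regulation of platelet reactivity". The Discussion (section 3) is more direct: "These observations prompt the hypothesis that PCSK9 may potentiate platelet reactivity via regulating ox-LDL-platelet interplay in the setting of ACS".

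The analyses are listed in the Abstract ("Spearman correlations will be used to determine association of serum PCSK9 with platelet functional parameters and platelet-ox-LDL binding") and in section 2.2.5 ("The association of PCSK9 levels with platelet reactivity and ox-LDL-platelet binding will be evaluated by Spearman rank test"). Section 2.2.5 adds PCSK9 tertiles and a regression step: "univariate and multivariate logistic regression will be used to analyze the association between PCSK9 levels with on-treatment platelet reactivity". Every association named has PCSK9 on one side.

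On how the mechanistic question will be addressed, the Discussion says: "To this end, the association of serum PCSK9 and platelet-ox-LDL binding, an important mechanism for platelet-ox-LDL interplay, will also be explored in ACS patients". The Conclusions (section 4) state that the PCSK9-binding relationship is intended "to provide mechanistic insight into PCSK9-mediated platelet activation", and that if results are positive "the observations would reinforce the concept of PCSK9-mediated modulation of platelet activation in a clinical setting".

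**The concern.** The rationale has three quantities in a chain: serum PCSK9, ox-LDL bound to platelets, and platelet reactivity. The analysis examines the first with the second and the first with the third. The link from the second to the third, which carries the word *via* in the hypothesis, is not examined in this cohort.

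If both planned correlations come out positive, the natural summary is that PCSK9 acts on platelets through ox-LDL binding. The same results would arise if PCSK9 were associated with binding and with reactivity for unrelated reasons. The stated limitations (single centre, limited sample size, cross-sectional design) do not mention this gap. At stake is the interpretation of the study's secondary, mechanistic message, not the validity of either planned test.

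**Working it through.** **Inputs from the protocol.** Recruitment of 115 with 20% attrition (Sample size section); two-sided alpha of 0.05 (section 2.2.5). Evaluable number: 115 × (1 − 0.20) = 92. The protocol does not state 92.

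**Inputs assumed.** The protocol gives no correlations. I write X for PCSK9, M for binding and Y for reactivity, and take r(XM) = r(XY), mainly at 0.30, with other values to show the range.

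**Step 1: do two correlations fix the third?** The admissible range is

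r(MY) = r(XM)·r(XY) ± √[(1 − r(XM)²)(1 − r(XY)²)].

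- Both 0.20: 0.04 ± 0.96, so −0.92 to 1.00.
- Both 0.30: 0.09 ± 0.91, so −0.82 to 1.00.
- Both 0.40: 0.16 ± 0.84, so −0.68 to 1.00.

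The planned results leave the binding-reactivity correlation almost unconstrained.

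**Step 2: what would that mean for the path?** On standardised scales the effect of binding given PCSK9 is b = [r(MY) − r(XM)·r(XY)] / [1 − r(XM)²]. The indirect effect is r(XM)·b, and its share of the total is r(XM)·b / r(XY). With both PCSK9 correlations at 0.30:

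| r(MY) | b | Indirect | Share of total |
|---|---|---|---|
| −0.30 | −0.39/0.91 = −0.429 | −0.129 | −43% |
| 0.09 | 0/0.91 = 0 | 0 | 0% |
| 0.30 | 0.21/0.91 = 0.231 | 0.069 | 23% |
| 0.70 | 0.61/0.91 = 0.670 | 0.201 | 67% |

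The same pair of planned correlations fits none, some or most of the association running through binding.

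**Step 3: how often would the two tests both be positive with no role for binding?** I simulated normal data with n = 92, M and Y independent given X, and Spearman tests at two-sided 0.05:

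| Each PCSK9 correlation | Both planned tests significant |
|---|---|
| 0.20 | about 20% |
| 0.30 | about 64% |
| 0.35 | about 83% |
| 0.40 | about 94% |

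**Step 4: would an added analysis discriminate?** This step uses Pearson correlations, n = 92 and 20,000 runs. The criterion is a significant PCSK9-binding correlation together with a significant PCSK9-adjusted binding-reactivity correlation. With no role for binding it is met in about 4% of studies (correlations of 0.30) to 5% (0.40). If binding does matter (b = 0.30, direct effect 0.21, total 0.21 + 0.30 × 0.30 = 0.30), it is met in about 69%.

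The adjustment is needed. With both PCSK9 correlations at 0.30 and no role for binding, the crude binding-reactivity correlation is still 0.30 × 0.30 = 0.09, and at 0.40 it is 0.16.

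**The case against.** The strongest reply is that aims and analyses match. The path sentence is rationale; the question the Discussion then sets is whether PCSK9 is involved in ox-LDL binding, and section 2.2.5 analyses exactly that. The language is also guarded: relationships are possible, the work is exploratory and preliminary, and pathways downstream of binding are left to later studies. This stands. A reader might infer that the study's declared aims go untested, or that the plan commits to announcing a mechanism. The documents support neither.

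The article also lists no covariates for its multivariable logistic model, and a covariate list may sit in an analysis plan not shown here. One therefore cannot say that binding is excluded from that model. The point does not depend on this: the article itself states both the mechanistic purpose and the association meant to serve it, and those two do not match.

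The percentages in Step 3 could be misread as a false-positive rate. They are the joint power to detect two associations that are true by assumption. Reading them as wrong conclusions needs a rule, both tests significant equals mechanism, that the protocol does not contain. At 0.20 the figure is only about 20%.

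The deferral to future work does not close the gap. What is deferred lies downstream of binding. Whether binding relates to reactivity at all is the prior question, and these patients' data can address it.

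**Conclusion.** The concern holds in this limited form: as stated, the analyses cannot tell a role for ox-LDL binding from two parallel PCSK9 associations, yet the Abstract, Discussion and Conclusions offer mechanistic insight on that basis. The logical gap does not depend on any assumed number. Its practical size does: the 20% to 94% range rests on assumed correlations of 0.20 to 0.40, 92 evaluable patients and conditional independence of binding and reactivity.

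No planned test is invalid, and recruitment and measurement are unaffected. The change is worth making before analysis because it decides what the mechanistic sentence may say.

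**What to change.** Add the following, labelled exploratory:

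1. Spearman correlations of platelet-bound ox-LDL with ADP-induced and arachidonic-acid-induced maximum aggregation, P-selectin and PAC-1.
2. Either a partial rank correlation of binding with reactivity adjusted for PCSK9, or a linear model of continuous ADP-induced aggregation on PCSK9 with and without binding, reporting the indirect effect with a bootstrap 95% confidence interval.

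Do not make the with-and-without comparison on the planned logistic model. Its PCSK9 coefficient can shift when binding is added even if there is no mediation.

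Tie any mechanistic statement to these results and word it as consistent with the path. If they are not added, limit the mechanistic wording in the Abstract, Discussion and Conclusions to two separate associations.

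The cost is a few more unadjusted exploratory tests and an indirect-effect interval that will be wide at this sample size; no new samples or visits are needed. Even then, a single sampling time cannot establish direction, rule out confounding or prove causal mediation.

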## 4. Conclusions

Several preclinical clues have suggested that beyond the role in LDL metabolism, PCSK may be involved in regulating of platelet function. To address the knowledge gaps, we aim to evaluate circulating PCSK9 levels and unravel its association with platelet reactivity in a Chinese ACS cohort. If positive results are obtained, the observations would reinforce the concept of PCSK9-mediated modulation of platelet activation in a clinical setting. Moreover, we will reveal possible relationship between PCSK9 level and ox-LDL-platelet binding, an important mechanism underlying ox-LDL-induced platelet hyperactivity, to provide mechanistic insight into PCSK9-mediated platelet activation.
